**(5) Survey planned at 3 months after the initiation of protocol treatment**

The following survey will be implemented at 3 months after the initiation date of protocol treatment:

① Physical findings

\* It is acceptable to implement the survey within 2 weeks before or after the specified day.

- A) Weight
- B) Performance status

② Diagnostic imaging for evaluation of breast cancer lesions

\* It is desirable to use the same techniques as those used for the examination implemented before registration.

\* It is recommended to implement the examination within 2 weeks before or after the specified day.

- A) Chest CT, MRI, or chest X-ray
- B) Abdominal CT, MRI, or abdominal ultrasound
- C) Bone scintigraphy when bone metastasis is clinically suspected
  - \* When bone metastasis is suspected by bone scintigraphy, bone radiography, CT, or MRI, etc. is conducted to further evaluate the lesion.
- D) Brain CT or MRI when brain metastasis is clinically suspected
- E) Evaluation and recording of lymph nodes and locally recurrent skin foci
  - \* Inspection: It is favorable to record progress using photographs with indicators attached.
  - \* Palpation: The size of foci such as superficial lymph nodes and cutaneous metastases will be directly measured from outside the body if their sizes are measurable. It is desirable to use CT and/or ultrasound for evaluations where applicable.

③ Survey of adverse events

The presence or absence of adverse events of Grade 3 or higher occurring within the past 3 months will be confirmed and recorded.

\* It is acceptable to implement the survey within 2 weeks before or after the specified day.

The contents of survey are the same as specified in ④ of 5.4 (3). The survey must be completed before registration.

④ Survey of treatment state

- A) Presence or absence of discontinuation of the protocol treatment and the reasons and date of discontinuation if discontinued
- B) Compliance with the protocol treatment for the past 3 months

- C) Presence or absence of use of bisphosphonate formulation or anti-RANKL antibody for the past 3 months
  - D) Presence or absence and reasons for implementation of concomitantly used therapies (surgical therapy for breast cancer focus, radiotherapy for breast cancer focus, any molecularly-targeted drugs other than mTOR inhibitors, chemotherapy, immunotherapy, other drugs recognized to have antitumor activity against breast cancer) for the past 3 months
- ⑤ Survey of HRQoL {the same as 5.4 (4) ①}
- (6) Survey plan at 6 months after the initiation of protocol treatment
- The following survey will be implemented at 6 months after the initiation day of protocol treatment:
- \* However, the survey at 6 months after the initiation is not required when discontinuation of the protocol treatment or progression is reported in the survey at 3 months after the initiation. Move to the survey detailed in (7) for such cases.
- ① Physical findings
- \* It is acceptable to implement the survey within 2 weeks before or after the specified day.
- A) Weight
  - B) Performance status
- ② Diagnostic imaging for evaluation of breast cancer lesions
- \* It is desirable to use the same techniques as those used for the examination implemented before registration.
- \* It is recommended to implement the examination within 2 weeks before or after the specified day.
- A) Chest CT, MRI, or chest X-ray
  - B) Abdominal CT, MRI, or abdominal ultrasound
  - C) Bone scintigraphy when bone metastasis is clinically suspected
    - \* When bone metastasis is suspected by bone scintigraphy, bone radiography, CT, or MRI, etc. will be conducted to further evaluate the lesion.
  - D) Brain CT or MRI when brain metastasis is clinically suspected
  - E) Evaluation and recording of lymph nodes and locally recurrent skin foci
    - \* Inspection: It is favorable to record progress using photographs with indicators attached.
    - \* Palpation: The size of foci such as superficial lymph nodes and cutaneous metastases will be directly measured from outside the body if their sizes are measurable. It is

desirable to use CT and/or ultrasound for evaluations where applicable.

③ Survey of adverse events

The presence or absence of adverse events of Grade 3 or higher occurring between the previous survey and the day of the current survey is confirmed and recorded.

\* It is acceptable to implement the survey within 2 weeks before or after the specified day.

The contents of survey are the same as specified in ④ of 5.4 (3). The survey must be completed before registration.

④ Survey of treatment state

- A) Presence or absence of discontinuation of the protocol treatment and the reasons and date of discontinuation if discontinued
- B) Compliance with the protocol treatment for the past 3 months
- C) Presence or absence of use of bisphosphonate formulation or anti-RANKL antibody for the past 3 months
- D) Presence or absence and reasons for implementation of concomitantly used therapies (surgical therapy for breast cancer focus, radiotherapy for breast cancer focus, molecularly-targeted drugs other than mTOR inhibitors, chemotherapy, immunotherapy, other drugs recognized to have antitumor activity against breast cancer) for the past 3 months

(7) Survey plan at 6 months or later after the initiation of protocol treatment or after discontinuation of the protocol treatment

① Timing of survey

- A) Every year from 6 months after the initiation of the protocol treatment when the protocol treatment is ongoing at the time of 6 months after the initiation of the protocol treatment
- B) Every year from the day of discontinuation of the protocol treatment when the protocol treatment is discontinued at the time of 6 months after the initiation of the protocol treatment

② Contents of survey

- A) Continuation state of protocol treatment: Presence or absence of continuation of the protocol treatment. If it is discontinued, the date and reasons for the discontinuation {only for subjects corresponding to the criteria specified in 5.4 (7) ①-A)}.
- B) Survey of progression: Presence or absence of progression defined in 3.9 (2). When progression was observed, the date when the progression occurred was determined (not required for a subject whose progression is already reported.)

- C) Survey of after-treatment: Presence or absence of implementation of chemotherapy. If chemotherapy is implemented, the date and type of chemotherapy.
- D) Survey of prognosis: The final confirmed day of survival. In case of death, the date and cause of death.

(8) Discontinuation of survey

When a case meets one of the following criteria, the survey will be discontinued.

- ① When it is determined that continuation of the rest of the survey is not possible due to changing hospital or other reasons
- ② Withdrawal of consent
- ③ Death
- ④ When it becomes clear that the eligibility criteria are not satisfied
- ⑤ Other reasons, when it is determined that continuation of the study as a subject is not possible

---

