#### (1) Evaluation duration of adverse events

The evaluation duration of adverse events in this study is from the registration to 30 days after the completion of the protocol treatment specified as the object of evaluation.

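### The month-3 adverse event survey looks back a fixed 3 months but may be done 2 weeks late, so its wording does not reach back to registration, where the protocol starts adverse event evaluation.

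*Protocol*

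**What the plan says.** **Month-3 adverse events, 5.4 (5) ③.** "The presence or absence of adverse events of Grade 3 or higher occurring within the past 3 months will be confirmed and recorded". The item adds: "It is acceptable to implement the survey within 2 weeks before or after the specified day". It closes with: "The survey must be completed before registration".

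**Month-6 adverse events, 5.4 (6) ③.** Here the period is tied to the last contact: "adverse events of Grade 3 or higher occurring between the previous survey and the day of the current survey is confirmed and recorded". The same closing sentence about registration is repeated.

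**Treatment state, 5.4 (5) ④ and 5.4 (6) ④, items B) to D).** Compliance, bone agents and added antitumour treatment are all asked over a fixed 3 months at both surveys, for example "Compliance with the protocol treatment for the past 3 months" and "other drugs recognized to have antitumor activity against breast cancer) for the past 3 months". No 2-week tolerance is printed under these items. In the schedule table of 5.4 (2), Note 4 is attached only to imaging and quality of life.

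**Evaluation period.** 19.1 (1) says that the adverse event evaluation duration "is from the registration to 30 days after the completion of the protocol treatment"; 3.9 (8) also starts at registration. Under 5.3 (1), treatment is to start within 2 weeks of registration, and a longer delay needs a recorded reason.

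**Other recording duties.** 19.1 (2) requires the name, worst grade and onset date of Grade 3 or higher events in the Progress report. 5.3 (5) requires added antitumour treatment to be described there, and 5.7 (3) lists adverse events and concomitant treatment among its contents. None of these carries a 3-month limit.

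**The concern.** A fixed look-back covers the time since treatment start only if the survey is done on or before its due day. The protocol allows it to be late, so the period that drops out is the first weeks on treatment. No other scheduled adverse event survey asks about those weeks: the table in 5.4 (2) has none at month 1, and the preceding one takes place before registration. Month 3 is therefore the first routine adverse event survey on treatment.

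At stake is the adverse event incidence by type and grade in all treated cases, a stated secondary outcome (5.10 (3)). Only Grade 3 or higher events are collected. If some sites apply the 3-month question literally and others record from registration, the incidence rests on unequal observation periods.

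**Working it through.** The protocol gives no figure to reproduce; the check is interval arithmetic.

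**Inputs.** Treatment start = day 0. The due days are taken as day 91 (month 3) and day 182 (month 6), an assumption. Tolerance is ±14 days (5.4 (5) ③). The look-back is 91 days. Treatment starts 0 to 14 days after registration (5.3 (1)).

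**Step 1: month-3 adverse event item.** First day covered = survey day − 91. Treatment days missed = max(0, first day covered). Days missed since registration, with treatment starting 14 days after it = max(0, first day covered + 14).

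| Month-3 survey | First day covered | Treatment days missed | Days missed since registration (14-day wait) |
|---|---|---|---|
| day 77 (14 early) | 77 − 91 = −14 | 0 | 0 |
| day 91 (on time) | 91 − 91 = 0 | 0 | 14 |
| day 105 (14 late) | 105 − 91 = 14 | 14 | 28 |

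In the last row, 14 of 105 treatment days (14/105 = 13%) lie outside the question. That is the maximum within the tolerance. Treatment days missed equal the days of lateness, so the choice of 91 days for 3 months does not matter. A wait longer than 2 weeks before treatment would add to the last column.

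**Step 2: month-6 adverse event item.** It starts at the previous survey, so the gap is 0 days for every combination of survey dates.

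**Step 3: treatment-state items, if they are collected at the same visits with the same tolerance (an inference).** Gap = max(0, (month-6 day − 91) − month-3 day).

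| Month-3 day | Month-6 day | Gap |
|---|---|---|
| 77 | 196 | (196 − 91) − 77 = 28 |
| 77 | 182 | (182 − 91) − 77 = 14 |
| 91 | 196 | (196 − 91) − 91 = 14 |
| 91 | 182 | (182 − 91) − 91 = 0 |
| 105 | 196 | (196 − 91) − 105 = 0 |

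The worst case is 28 of the 119 days between surveys (196 − 77 = 119; 28/119 = 24%). It needs month 3 at its earliest and month 6 at its latest.

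**Step 4: after rewording.** If month 3 is anchored to registration (adverse events) or treatment start (treatment state), and month 6 to the previous survey, the uncovered time is 0 days in every combination.

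**The case against.** The strongest reply is that the look-back wording does not govern what is collected. 19.1 (1) and 3.9 (8) start evaluation at registration, 19.1 (2) requires every Grade 3 or higher event with its onset date, and 19.2 makes Grade 3 and 4 events reportable. 5.3 (5) and 5.7 (3) do the same for added antitumour treatment. The report on initiation of treatment, due within 2 weeks of the start (5.6), also has adverse event and concomitant drug items (5.7 (2)). On this view the month-3 phrase is a loose description, and the 14 and 28 days are corner cases.

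Much of this stands. A reader might infer that early events fall where nothing captures them; the duties just listed rule that out. A reader might also infer that unrecorded added therapy distorts the count of patients with clinical benefit. It cannot: 3.9 (1) defines benefit by imaging response and absence of clinical progression, concomitant treatment is not prohibited (5.3 (1)), and no rule reclassifies patients for it.

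The reply does not remove the conflict. The Progress report is the form completed for these same 3- and 6-month surveys (5.6), and ordinary Grade 3 and 4 events enter it at its normal submission time (19.2 (3)), so it is not an independent safeguard. Urgent reporting under 19.2 (1) covers deaths and unknown non-haematological toxicity, not known Grade 3 or 4 toxicity. The initiation report states no look-back and can be filed before the first 2 weeks of treatment are over. A site thus has two instructions for one form.

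The closing sentence about registration may be a garbled pointer to 5.4 (3), whose heading concerns the pre-registration survey. As printed it cannot be met by a survey 3 or 6 months into treatment, but correcting it is editorial.

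**Conclusion.** The month-3 adverse event look-back is inconsistent with the protocol's own evaluation period, with its open-ended duty to record, and with its month-6 wording. Read literally, it leaves out up to 14 treatment days when the survey is late. Counted from registration it leaves out up to 14 days when the survey is on time and up to 28 when it is late, given a treatment start within 2 weeks. Early and on-time surveys miss no treatment days.

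The consequence is a risk that early Grade 3 or higher events are under-recorded or recorded differently by site. Loss of data is not shown, and how many events would be affected cannot be derived from the document. The primary clinical benefit rate and its test are unaffected.

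The 0 to 28 day gap in the treatment-state items is conditional on those items sharing visits and tolerance with the others. It concerns the description of treatment, which 5.3 (5) and 5.7 (3) require in the Progress report anyway. The defect is modest, but it bears on a stated outcome and is easily removed.

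**What to change.** - 5.4 (5) ③: ask about Grade 3 or higher events *since registration*. The onset date already required by 19.1 (2) separates events before treatment from those on treatment.
- 5.4 (5) ④ B) to D): for consistency, ask about the period *since the initiation of protocol treatment*.
- 5.4 (6) ④ B) to D): ask about the period *since the previous survey*, matching the rule already used in 5.4 (6) ③.
- Editorial: delete the sentence "The survey must be completed before registration" from 5.4 (5) ③ and 5.4 (6) ③.

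The cost is a wording change in 5.4 and in the matching questions of the Progress report. No visit or data item is added.

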## 5.5 Survey of health-related quality of life

### (1) Background of HRQoL evaluation

Health-related quality of life (HRQoL) is generally defined as the effect of diseases and treatment on health and the entirety of life . Usually HRQoL is a multidisciplinary concept consisting of basic domains including functional, physical, mental, and social aspects and emphasizes the subjective experience of the patient as the central point of evaluation. Recently, it has become clear that there can be a great dissociation between subjective evaluation by medical staff and that by patients even for single areas such as individual symptoms or signs. As a result, HRQoL emphasizes the subjective experience of patients even for evaluations of single areas . In the context of that background, the concept of patient-reported outcomes (PROs) as a more comprehensive subjective evaluation framework including HRQoL and symptoms in the area of health was established. Furthermore, various scales that have been validated for their reliability and validity for measuring PROs have been developed following the establishment of the concept of PROs. In 2012, the American Society of Clinical Oncology (ASCO) published "Recommendations for incorporating patient-reported outcomes into clinical comparative effectiveness research in adult oncology", and stated that the evaluation of PROs is essential to obtain information useful for making decisions about a patient in clinical comparative studies of adult cancer, especially those of intractable metastatic cancer . Metastatic breast cancer, which is the subject of this study, is intractable even using current medical treatment, and it is considered that the main purposes of treatment in such cases are the extension of survival time, maintenance and improvement of HRQoL, and alleviation of symptoms .

### (2) Objectives of HRQoL evaluation

The major objective of this study is to evaluate the efficacy and safety of recent endocrine therapies for breast cancer with low sensitivity to the primary endocrine therapy. The maintenance and improvement of QoL is a key objective in the treatment of metastatic breast cancer, and evaluation of QoL is essential for the evaluation of the efficacy of treatments. HRQoL is often discussed as differences and changes in scores obtained by the statistical analysis of questionnaire data. However, it is critical to understand the clinical significance of any differences and changes in such scores. Recently, the concept of minimally important difference (MID) has been emphasized as an index to understand HRQoL scores. MID represents the clinically meaningful minimum difference in the HRQoL scores, and validation of MID is indispensable for the meaningful evaluation of HRQoL in clinical cancer research.

As mentioned above, objectives of the HRQoL evaluation in this study are as below:

- ① To clarify the effect of secondary endocrine therapy on estrogen receptor-positive, HER2-negative postmenopausal metastatic breast cancer for which the primary endocrine therapy had no favorable clinical effect (low sensitivity to primary endocrine therapy) on HRQoL using HRQoL maintenance rate, which is a clinically meaningful index.

- ② To clarify the clinical significance inherent in HRQoL score values as the minimally important differences (MIDs) associated with endocrine therapy for metastatic breast cancer by focusing attention on variations in HRQoL scores obtained for subjects of this study over time.

(3) HRQoL scales

The following scales are used (Appendix F).

In addition, a questionnaire survey related to the social background and expectancy of QoL of patients, which may have an impact on subsequent HRQoL scores, will be conducted at the time of registration.

- ① (Functional Assessment of Cancer Therapy) ES (Endocrine Symptoms, 19 items) and B (Breast, 10 items) as additional QOL scales, FACT-G (General, 27 items, Japanese version), which is a scale generally used for clinical studies of cancer.
- ② Questions about changes: Used as subjective anchoring information required for identification of MIDs (minimally important differences).

(4) Survey schedule

| Survey term                                                | At registration
<small>Note 1</small>                                                              | 1 month after the initiation of protocol treatment
<small>Note 2</small> | 3 months after the initiation of protocol treatment
<small>Note 2</small> |
|------------------------------------------------------------|-------------------------------------------------------------------------------------------------------|-----------------------------------------------------------------------------|------------------------------------------------------------------------------|
| Social background                                          | ○                                                                                                     |                                                                             |                                                                              |
| Expectancy of QoL                                          | ○                                                                                                     |                                                                             |                                                                              |
| FACT-G, -B, -ES                                            | ○                                                                                                     | ○                                                                           | ○                                                                            |
| Questions about changes                                    |                                                                                                       | ○                                                                           | ○                                                                            |
| Survey of medical staff about the reasons for missing data | When the questionnaire is not sent back from the subjected patient after the scheduled survey period. |                                                                             |                                                                              |

Note 1: It is desirable to complete the survey at the time of registration between the acquisition of consent and the completion of registration.

When there is insufficient time, the survey should be completed before the initiation of the protocol treatment.

Note 2: It is acceptable to implement the survey within 2 weeks before or after the specified day.

(5) HRQoL survey for patients who discontinued the protocol treatment

Evaluation of HRQoL will be discontinued when the protocol treatment is discontinued due to disease progress, development or exacerbation of complications, or adverse events.

(6) Survey method

- ECOG PS will be determined by a clinical investigator at the same time as the QoL survey is conducted using specified survey terms and the results will be described in the Progress report.
- When the patient cannot complete the questionnaire due to an exacerbation of the disease condition of the patient, it is acceptable to implement the survey by reading the questionnaire by the Clinical Research Coordinator (CRC).

(7) Survey of reasons for missing data

When the questionnaire is not sent back for a patient after the scheduled survey period (5.5 (4) ), the data center surveys the reasons for the missing data, including the situation of questionnaire distribution and the health condition of the subject by asking the responsible clinical investigator. The reasons for missing data are classified as below, and described as profiles of the study subject in the statistical analysis report and publications of the study results (conference presentations and paper publications).

- ① Exacerbation of disease condition of the subject
- ② Death of the subject
- ③ Rejection of the survey by the subject
- ④ Forgetfulness of the subject in completing and returning the questionnaire or loss of the questionnaire
- ⑤ Reasons associated with factors caused by the subject other than the above
- ⑥ Forgetfulness of distribution of the questionnaire from a person in charge to the subject

(8) Number of patients scheduled to undergo HRQoL survey

All of the subjects registered into this study are subjects of the survey.

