- PgR positive group: PgR positive (J-score classification is 1% or higher)

Analyses of secondary outcomes will also be conducted on a by-cohort basis. For RR defined by a 2-value endpoint response, an accurate 90% confidence interval based on point estimation and the binomial distribution is calculated. Furthermore, for PFS, OS, TTF, and TTC, which are time-to-event outcomes, a survival curve will be estimated using a Kaplan-Meier method, and 90% confidence intervals of the survival rate at each event will be calculated using Greenwood's formula. The interaction effect will be analyzed for effect predictors in the same manner as that used for the primary outcomes.

Analysis of adverse events will be performed in all treated cases. Incidence rate by types and grade will be calculated for reported adverse events.

③ Analysis of HRQoL

FACT-G, Breast, and ES, which are calculated as total scores, will be calculated for the aggregate score and subdomain scores in accordance with a scoring manual to calculate the fundamental statistics at the time of each survey for all subjects.

Furthermore, cases with decreases in scores exceeding the threshold values as compared with scores at the registration will be individually identified and the maintenance rate of QoL will be calculated using MIDs identified by scales as a meaningful threshold value of decrease of QoL score at each measurement point.

Information obtained from questions about changes will be used as subjective anchoring information required for the identification of MID during the endocrine therapy, and differences from the previously established MID will be examined.

Since it is considered that the evaluation and analysis of HRQoL have no influence on the clinical benefit rate, which is the primary outcome measures of this study, analysis will be implemented immediately after the data collection (after the collection of QoL questionnaires at 3 months for the last registered case). The results of the analysis will be published as conference presentations and papers.

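### HRQoL collection stops when treatment stops for progression, complications or adverse events, so the month-3 maintenance rate is an on-treatment measure and probably too high for the stated HRQoL objective

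*Protocol*

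**What the plan says.** Section 5.5 (2) ① of the protocol sets the aim: "To clarify the effect of secondary endocrine therapy on estrogen receptor-positive, HER2-negative postmenopausal metastatic breast cancer", with respect to HRQoL, "using HRQoL maintenance rate, which is a clinically meaningful index". Section 5.5 (8) defines who is surveyed: "All of the subjects registered into this study are subjects of the survey". Questionnaires are planned at registration and at 1 and 3 months after treatment starts (5.4 (1), 5.5 (4)).

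Section 5.5 (5) then limits collection: "Evaluation of HRQoL will be discontinued when the protocol treatment is discontinued due to disease progress". The same sentence lists complications and adverse events as further triggers. Stopping for other reasons, such as refusal, is not named.

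Section 5.10 (3) ③ first describes how losses are found: "cases with decreases in scores exceeding the threshold values as compared with scores at the registration will be individually identified". It then defines the summary measure in these terms: "the maintenance rate of QoL will be calculated using MIDs identified by scales as a meaningful threshold value". The calculation is made at each measurement point. No denominator is stated, and nothing says how to count a patient whose questionnaires ended under 5.5 (5). Section 5.5 (7) has the reasons for unreturned questionnaires classified and described, but does not use them in the rate.

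**The concern.** The three reasons that end collection are the ones most likely to go with worse HRQoL, so whether a score is missing depends on the thing being measured. Section 3.8 (4) itself expects that some patients will worsen soon after starting treatment, which falls inside the three-month HRQoL window.

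The result would be presented as the effect of therapy on HRQoL in the target population, while describing mainly those whose treatment had not been stopped for these reasons. Section 5.10 (3) ③ also plans to analyse and publish HRQoL as soon as the last month-3 questionnaires are in. A SAP could redefine the denominator, but it cannot recover scores that the protocol says not to collect.

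Objective ② in 5.5 (2) is touched as well. The change questions anchor the MID, and the rule thins the group of patients who would report being worse.

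**Working it through.** **Plan's own figure.** The protocol gives no figure for the maintenance rate. The nearest figure is the sample size in section 7.3: 43 per cohort for a clinical benefit rate (CBR) of 30% against 50%, exact binomial test, one-sided 5%, 80% power. It reproduces: with n = 43 and success at 19 or more, the error rate is 0.034 and the power 0.820. It does not bear on HRQoL, but it supplies the two CBR values used below.

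**Inputs from the protocol**
- CBR: the proportion without progression for 6 months from the start of treatment (3.9 (1)); threshold 30%, expected 50% (7.3).
- HRQoL after baseline: months 1 and 3.
- Target enrolment: 200 or more (5.9).

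**Assumptions, not in the protocol**
- Constant hazard of progression, and every progression ends treatment and the survey at once.
- Maintenance on treatment m_on = 70%; maintenance after stopping m_off = 0% to 40%.

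**Step 1: share progressed by month t.** f(t) = 1 − CBR^(t/6).
- Month 1: 1 − 0.50^(1/6) = 0.11; 1 − 0.30^(1/6) = 0.18.
- Month 3: 1 − √0.50 = 0.29; 1 − √0.30 = 0.45. Of 200 patients, that is about 59 to 90.

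This counts progression only. Stops for complications or adverse events would add to it. Patients who stay on treatment after progression, or whose progression is first found at the 3-month scan, would reduce it.

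**Step 2: month-3 rate in all patients.** True rate = (1 − f) × m_on + f × m_off.

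| f | m_off | True rate | Available-case rate | Excess, f × (m_on − m_off) |
|---|---|---|---|---|
| 0.29 | 0 | 0.497 | 0.70 | 0.203 |
| 0.29 | 0.40 | 0.613 | 0.70 | 0.087 |
| 0.45 | 0 | 0.385 | 0.70 | 0.315 |
| 0.45 | 0.40 | 0.565 | 0.70 | 0.135 |
| either | 0.70 | 0.70 | 0.70 | 0 |

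The excess is about 9 to 32 points, and zero if stopped patients do as well as the others.

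**Step 3: the other literal reading of 5.10 (3) ③.** Stopped patients stay in the denominator but, having no score, are never flagged as decreased. The rate is (1 − f) × 0.70 + f, which is 0.787 for f = 0.29 and 0.835 for f = 0.45. The excess is f × (1 − m_off): from 0.29 × 0.60 = 0.174 to 0.45 × 1 = 0.45.

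**Step 4: stopped patients counted as not maintained.** The rate is (1 − f) × 0.70, which is 0.497 or 0.385. If 40% of stopped patients in fact keep their HRQoL, this lies below the true rate by f × 0.40: 0.116 to 0.18, or about 12 to 18 points. It is a different estimand, not a correction to the truth.

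**The case against.** The strongest reply is that the protocol fixes no denominator. Denominators and missing-data rules for a secondary outcome commonly belong in the SAP, which is not shown. That stands: the missing denominator is not in itself a fault. It does not reach the collection rule, which is a protocol decision. As the text is written, both natural readings of 5.10 (3) ③ lean upward if HRQoL is worse after these stops.

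Other replies are fair in part:
- A reader might infer that the rate covers only patients who are doing well. The text does not support this. Patients whose HRQoL falls while on treatment are still surveyed, and 5.5 (6) lets a coordinator read the questionnaire to those whose condition has worsened.
- A reader might infer that anyone who progresses before month 3 can never be counted as a loss. The trigger is stopping treatment, not progression, and a decline at month 1 counts at month 1.
- A reader might take the gap between the on-treatment rate and a rate that scores every stopped patient as a failure, and call it bias. That gap compares two estimands, and its size is set by the assumed on-treatment rate.
- The described reasons for missing questionnaires warn readers, but leave the rate unchanged.
- Few surveys were chosen to limit burden (5.1 (1), section 11). The remedy stays within the three already planned.
- Section 5.10 (3) ③ wants the MID for the period of endocrine therapy. Ratings made after stopping could reflect later treatment and should not be mixed in. This stands and shapes the fix.

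**Conclusion.** The concern holds as a matter of mechanism and direction. Collection ends for reasons linked to worse HRQoL, and non-maintenance needs an observed decrease, so the month-3 rate is an on-treatment measure that does not answer objective ① for the registered population. The direction rests on HRQoL being worse after such stops, and on no unseen SAP rule that counts these patients as not maintained.

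The size cannot be derived from the documents. The 9-32 points are an illustration that depends on the constant hazard and the assumed maintenance rates. The 29-45% is best read as an upper guide to the loss from progression. HRQoL is a secondary outcome, and the CBR analysis does not depend on it. The change is worth making because it is cheap and cannot be made after the data are in.

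**What to change.** 1. In 5.5 (5), send the month-1 and month-3 questionnaires to every living, consenting patient, whether or not protocol treatment continues.
2. In 5.10 (3) ③, calculate the maintenance rate over all treated patients with a baseline score. Count as not maintained those who died, and those who stopped for progression, complications or adverse events and have no later score.
3. Report the on-treatment rate as a second summary, labelled as such.
4. Base the MID anchoring on on-treatment ratings, or analyse ratings made after stopping separately.

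The cost is at most two further questionnaires of about 15 minutes for a patient who stops early, inside the planned total of three. Patients already remain in follow-up after stopping (5.4 (7)). Some scores will reflect next-line therapy, which the protocol leaves open. The composite rate will look less favourable and must be described as a composite.
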